### **Intention to vaccinate**

Intention to vaccinate will be assessed by comparing participants' responses to the question "Do you want to get a JE vaccine before your upcoming trip?" in both the pre- and post-intervention surveys. This question is based on the WHO's Behaviour and social drivers of vaccination survey priority questions. Responses will be categorised into four groups: 1) those who don't want to get vaccinated, 2) those who are not sure, 3) those who intend to get vaccinated and 4) those who are already vaccinated. The primary outcome will be the change in the proportion of participants who express an intention to get vaccinated before their trip, comparing the intervention group to the control group.

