### **Vaccine uptake**

For participants who consent to the follow-up survey, uptake of JE vaccine will be assessed through self-reported responses to the question, "Did you receive a vaccine for Japanese encephalitis before your trip?". While this approach relies on self-reported data rather than clinical records, it is a pragmatic choice given the research team's capacity and the limitations of the Australian Immunisation Register, which does not require mandatory reporting of non-National Immunisation Program vaccines for adults. Additionally, it minimises participant burden and preserves anonymity.

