## 2.9 Secondary Outcome 2: Intention to vaccinate

*Null hypothesis:* The online JE vaccine decision aid (JEVaDA) does not lead to a greater increase in participants' intention to get vaccinated before their trip compared to standard online health information among Australian adults planning overseas travel to JE risk areas.

*Research question:* Does use of JEVaDA lead to a greater increase in participants' intention to get vaccinated before their trip compared to standard online health information among Australian adults planning overseas travel to JE risk areas?

Intention to vaccinate will be assessed by the change in response to the question "Do you want to get a JE vaccine before your upcoming trip?". This question will be asked in both the pre-intervention and post-intervention surveys. Response options include: "No, I do not want to", "Yes, I

do want to”, “I am not sure”, and “I am already vaccinated”. For analysis, responses will be recoded into a binary variable, where “Yes, I do want to” is coded as 1, and all other responses are coded as 0. A new binary outcome variable will be created to capture positive change, defined as a shift from 0 pre-intervention to 1 post-intervention.

This outcome will be analysed using multivariable logistic regression. The dependent variable will be whether participants demonstrated a positive change in intention to vaccinate, and the primary independent variable will be group allocation. Baseline (pre-intervention) intention to vaccinate, age and sex will be included as covariates to adjust for baseline differences. Findings will be reported as adjusted odds ratios (ORs) with 95% confidence intervals (CIs) and p-values to indicate the strength and significance of the associations (Table 6).

**Table 6.** Logistic regression analysis of intention to vaccinate

| Variable                                 | Adjusted odds ratio (aOR) | 95% CI | p-value |
|------------------------------------------|---------------------------|--------|---------|
| Intervention group
(reference=JEVaDA) |                           |        |         |
| Baseline intention to
vaccinate       |                           |        |         |
| Age                                      |                           |        |         |
| Female sex                               |                           |        |         |

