### **Secondary Outcome 3: JE vaccine uptake**

*Null hypothesis:* The online JE vaccine decision aid (JEVaDA) does not lead to a greater increase in pre-travel JE vaccine uptake compared to standard online health information (HealthDirect fact sheet) among Australian adults planning overseas travel to JE risk areas.

*Research question:* Does use of JEVaDA lead to a greater increase in pre-travel JE vaccine uptake compared to standard online health information (HealthDirect fact sheet) among Australian adults planning overseas travel to JE risk areas?

JE vaccine uptake will be measured through self-reported responses to the question, "Did you receive a vaccine for Japanese encephalitis before your trip?" in an optional follow-up survey. Responses will be coded as 1 for “Yes” and 0 for “No” or “I don’t remember”.

This outcome will be analysed using multivariable logistic regression. The dependent variable will be self-reported JE vaccine uptake (binary) and the primary independent variable will be group allocation. As intention has been shown to be strongly associated with actual uptake and may confound the relationship between intervention and uptake, post-intervention intention to vaccinate will be included as a covariate, alongside age and sex. Findings will be reported as adjusted odds ratios (aORs) with 95% CIs and p-values (Table 7).

**Table 7.** Logistic regression analysis of JE vaccine uptake

| Variable                                 | Adjusted odds ratio (aOR) | 95% CI | p-value |
|------------------------------------------|---------------------------|--------|---------|
| Intervention group
(reference=JEVaDA) |                           |        |         |
| Post-intervention intention              |                           |        |         |

|              |  |  |  |
|--------------|--|--|--|
| to vaccinate |  |  |  |
| Age          |  |  |  |
| Female sex   |  |  |  |

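### The protocol's between-arm contrast in the proportion intending vaccination is never estimated, and the SAP gives no absolute effect for either intention or uptake

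*Combined protocol and SAP*

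**What the plan says.** **Intention, protocol.** Section 5.7.2 sets the outcome as the "change in the proportion of participants who express an intention to get vaccinated before their trip, comparing the intervention group to the control group". That is a contrast of proportions. Section 5.10 specifies only the decisional conflict model and gives no analysis for secondary outcomes.

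**Intention, SAP 2.9.** Yes is coded 1 and every other answer 0. Then: "A new binary outcome variable will be created to capture positive change, defined as a shift from 0 pre-intervention to 1 post-intervention". The model is logistic: "Baseline (pre-intervention) intention to vaccinate, age and sex will be included as covariates to adjust for baseline differences". Reporting is stated as: "Findings will be reported as adjusted odds ratios (ORs) with 95% confidence intervals (CIs) and p-values". Table 6 has columns for the adjusted odds ratio, its interval and the p-value only, and its group row is marked "reference=JEVaDA".

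**Uptake.** In the protocol, "uptake of JE vaccine will be assessed through self-reported responses to the question" asked at follow-up; no effect measure is named. In the SAP (Secondary Outcome 3) the logistic model contains group, post-intervention intention, age and sex: "Findings will be reported as adjusted odds ratios (aORs) with 95% CIs and p-values". Table 7 has the same columns and the same reference group as Table 6.

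SAP 2.6 does plan group means with intervals for the decisional conflict score. Nothing comparable is planned for the two binary outcomes.

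**The concern.** A reader of the protocol expects an answer of the form: the share wanting vaccination rose by so many points more with JEVaDA than with the fact sheet. The SAP cannot produce that sentence. An odds ratio does not convert to a difference in proportions without by-arm rates, and the SAP does not plan to tabulate them. For intention the dependent variable also differs: the protocol's change in a proportion nets losses against gains, while the SAP's variable counts gains only. For uptake, the model conditions on a variable that the aid is meant to change, so its group coefficient is not the total effect of being given the aid.

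**Working it through.** **1. Plan's own figure.** The documents give no expected rates and no numerical target for intention or uptake. The sample size in SAP 2.5 concerns the decisional conflict score and does not bear on this point. All rates below are therefore assumptions.

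**2. An odds ratio does not fix the absolute effect.** With pJ and pH the JEVaDA and HealthDirect proportions, RD = pJ - pH, RR = pJ/pH and OR = [pJ/(1-pJ)]/[pH/(1-pH)].

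| HealthDirect to JEVaDA | RD (points) | RR | OR | OR with JEVaDA as reference |
|---|---|---|---|---|
| 10% to 20% | 10 | 2.00 | 2.25 | 0.44 |
| 20% to 30% | 10 | 1.50 | 1.71 | 0.58 |
| 30% to 40% | 10 | 1.33 | 1.56 | 0.64 |

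The same 10-point gain gives three different odds ratios.

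**3. The shift variable is not the protocol's quantity.** Let b be the share answering Yes at baseline, g the share of the others who move to Yes, and l the share of baseline Yes who leave it. Net change in an arm = (1-b)g - bl. Take b = 30% and g = 30% (JEVaDA) v 20% (HealthDirect). Gains are 0.7 x 0.30 = 21 points v 0.7 x 0.20 = 14 points. The shift odds ratio among baseline non-Yes is (0.30/0.70)/(0.20/0.80) = 1.71, whatever the losses are.

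| l, JEVaDA v HealthDirect | Net change, JEVaDA | Net change, HealthDirect | Protocol contrast | Shift OR |
|---|---|---|---|---|
| 10% v 10% | 21 - 3 = 18 | 14 - 3 = 11 | +7 | 1.71 |
| 33.3% v 10% | 21 - 10 = 11 | 14 - 3 = 11 | 0 | 1.71 |
| 40% v 10% | 21 - 12 = 9 | 14 - 3 = 11 | -2 | 1.71 |

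**4. Baseline Yes participants carry no information in the SAP's model.** Someone coded 1 at baseline cannot move from 0 to 1, so the outcome is 0 for all of them. In one simulated data set of 350, there were 0 events among 104 baseline Yes and 69 among 246 others. The baseline-intention coefficient diverged (-25.7, standard error about 60,000). The group coefficient, 0.4605, was identical to the one fitted in the 246 alone.

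**5. Conditional and whole-arm odds ratios on the shift variable.** Take b = 30%, HealthDirect gains of 15% and a conditional odds ratio of 2.0. JEVaDA gains are then 26.1%. Over whole arms this is 0.7 x 15% = 10.5% v 0.7 x 26.1% = 18.3%: a difference of 7.8 points and a marginal odds ratio of (0.183/0.817)/(0.105/0.895), about 1.90. Table 6 would print the conditional value as 1/2.0 = 0.5.

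**6. Uptake.** Suppose the aid acts wholly through intention: 50% v 35% intend to vaccinate, and uptake is 40% among intenders and 5% among others in both arms. JEVaDA: 0.50 x 0.40 + 0.50 x 0.05 = 22.5%. HealthDirect: 0.35 x 0.40 + 0.65 x 0.05 = 17.25%. The total difference is 5.25 points and the total odds ratio is (0.225/0.775)/(0.1725/0.8275) = 1.39. Within each level of intention the arms are identical, so the SAP's adjusted odds ratio is 1.00.

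**The case against.** A prespecified adjusted odds ratio with a 95% interval is a legitimate between-group analysis of a secondary binary outcome, and the SAP commits to CONSORT reporting in section 1.2, so by-arm figures might appear anyway. The first part stands: the issue is a missing estimate. The second does not close the gap, because the SAP names no absolute measure, no model for it and no interval.

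A reader might go further and infer that the odds ratios will overstate the effect. The documents do not support that.
- An odds ratio and a risk difference are on different scales, so neither overstates the other. The inference needs the odds ratio to be misread as a risk ratio and the outcome to be common. The ratio of OR to RR is about 1.06 for rates between 5% and 15%, and reaches 1.33 to 1.43 only for rates between 40% and 65%. No rates are given, and the protocol's introduction describes JE vaccine uptake among travellers as low.
- With JEVaDA as reference, a benefit prints below 1.
- Once the intention model is in effect confined to baseline non-Yes, only age and sex separate the conditional from the marginal odds ratio in that group. If they contribute a logit standard deviation of 0.3 to 0.5, a conditional 2.00 becomes 1.92 to 1.98.
- For uptake the error can run the other way, as step 6 shows.

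Nor does the protocol set a contrast in proportions for uptake. The mismatch between protocol and SAP concerns intention alone; for uptake the gap is in what the SAP can show.

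**Conclusion.** For intention, the protocol's contrast in the change in proportion has no matching estimate in the SAP. The larger cause is the 0-to-1 shift variable, which ignores moves out of Yes; reporting only an odds ratio adds to it. In the assumed example one odds ratio, 1.71, is compatible with +7, 0 or -2 points on the protocol's scale. For uptake, the only planned estimate conditions on post-intervention intention and cannot show the total absolute effect. In the full-mediation example it reads 1.00 against a true difference of 5.25 points. These sizes rest wholly on assumed rates; the finding that the quantities are absent rests on the text alone. No general claim of overstatement is justified. Both are secondary outcomes and the primary analysis is unaffected, but the SAP should be amended.

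**What to change.** 1. **Intention (SAP 2.9, Table 6).** Fit a logistic model of post-intervention Yes on group, baseline intention, age and sex. Report the proportion by arm and the standardised risk difference, JEVaDA minus HealthDirect, with 95% CI, and keep the adjusted odds ratio beside it. Randomisation makes the baseline proportions equal in expectation, so this difference targets the protocol's contrast in change. In the first row of step 3 it is (0.27 + 0.21) - (0.27 + 0.14) = 7 points. Standardising the existing shift model would not do: it still ignores losses, and baseline Yes participants cannot have the event.
2. **Uptake (Secondary Outcome 3, Table 7).** Add the proportion by arm and the risk difference with 95% CI. It can be crude with a Newcombe interval, or standardised from a model with age and sex but without post-intervention intention. State the denominator, since the follow-up questionnaire does not put the vaccine question to every respondent.
3. **Direction.** State in both tables that the difference is JEVaDA minus HealthDirect, because the odds ratio rows use JEVaDA as reference.

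SAP Section 3 describes version 3 as final before data analysis. If analysis has begun, log these as dated additions. The cost is some added SAP text, a little more analysis and longer tables, with no new data. The absolute effect may look less striking than an odds ratio.

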### **Secondary Outcome 3: JE vaccine uptake**

*Null hypothesis:* The online JE vaccine decision aid (JEVaDA) does not lead to a greater increase in pre-travel JE vaccine uptake compared to standard online health information (HealthDirect fact sheet) among Australian adults planning overseas travel to JE risk areas.

*Research question:* Does use of JEVaDA lead to a greater increase in pre-travel JE vaccine uptake compared to standard online health information (HealthDirect fact sheet) among Australian adults planning overseas travel to JE risk areas?

JE vaccine uptake will be measured through self-reported responses to the question, "Did you receive a vaccine for Japanese encephalitis before your trip?" in an optional follow-up survey. Responses will be coded as 1 for “Yes” and 0 for “No” or “I don’t remember”.

This outcome will be analysed using multivariable logistic regression. The dependent variable will be self-reported JE vaccine uptake (binary) and the primary independent variable will be group allocation. As intention has been shown to be strongly associated with actual uptake and may confound the relationship between intervention and uptake, post-intervention intention to vaccinate will be included as a covariate, alongside age and sex. Findings will be reported as adjusted odds ratios (aORs) with 95% CIs and p-values (Table 7).

**Table 7.** Logistic regression analysis of JE vaccine uptake

| Variable                                 | Adjusted odds ratio (aOR) | 95% CI | p-value |
|------------------------------------------|---------------------------|--------|---------|
| Intervention group
(reference=JEVaDA) |                           |        |         |
| Post-intervention intention              |                           |        |         |

|              |  |  |  |
|--------------|--|--|--|
| to vaccinate |  |  |  |
| Age          |  |  |  |
| Female sex   |  |  |  |

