### 5.1.1. SELECTION CRITERIA

In order to be considered eligible to participate in this study, participants must be:

- Age 18 years or older
- Currently living in Australia
- Able to read and understand English
- Planning travel to a JE-endemic region within the next 6-months

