## Vaccination for Japanese encephalitis (JE)

**This group of questions asks you specifically about JE vaccines.**

Have you **ever** had a conversation with a healthcare professional about Japanese encephalitis (JE) vaccines?

|          |                          |
|----------|--------------------------|
| Yes      |  |
| No       |  |
| Not sure |  |

Have you ever received a JE vaccine?

- ☐ No
- ☐ Yes → answer next two questions
- ☐ Not sure

If yes, Which JE vaccine did you receive?

- ☐ Imojev (live-attenuated)
- ☐ JEspect (inactivated) vaccine
- ☐ Not sure

If yes, How many doses did you receive?

- ☐ One dose
- ☐ Two doses
- ☐ Not sure

How important do you think getting a JE vaccine is for your health?

- ☐ Not at all important
- ☐ A little important
- ☐ Moderately important
- ☐ Very important

How safe do you think getting a JE vaccine is for you ?

- ☐ Not at all safe
- ☐ A little safe
- ☐ Moderately safe
- ☐ Very safe

How much do you trust the health workers who would give you a JE vaccine?

- ☐ Not at all
- ☐ A little
- ☐ Moderately
- ☐ Very much

Do you think most of your close family and friends would want you to get a JE vaccine?

- ☐ No
- ☐ Yes

818 Do you know where to go to get a JE vaccine for yourself?

819 ☐ No

820 ☐ Yes

821

822 How easy is it to pay for JE vaccination? When you think about the cost, please consider the cost of  
823 the vaccine (up to \$300), would you say...

824 ☐ Not at all easy

825 ☐ A little easy

826 ☐ Moderately easy

827 ☐ Very easy

828

829 How easy is it for you to pay for other costs associated with JE vaccination? (e.g., any payments to  
830 the clinic, the cost of getting there and the cost of taking time away from work)

831 ☐ Not at all easy

832 ☐ A little easy

833 ☐ Moderately easy

834 ☐ Very easy

835

836

837 Do you want to get a JE vaccine before your upcoming trip?

838 ☐ No, I do not want to

839 ☐ Yes, I do want to

840 ☐ I am not sure

841 ☐ I am already vaccinated

842

843 **Based on your choice for your upcoming trip, please answer the following questions:**

844

|                                                                 | Strongly Agree | Agree | Neither Agree nor Disagree | Disagree | Strongly Disagree |
|-----------------------------------------------------------------|----------------|-------|----------------------------|----------|-------------------|

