### 1.2 General principles

Analysis and reporting of results will follow the CONSORT guidelines.[1] Baseline characteristics will be tabulated by intervention group (JEVaDA) and comparator group (HealthDirect JE fact sheet) using appropriate summary statistics. Data will be derived from those patients who meet inclusion criteria (currently living in Australia, aged 18 years or older, able to read and understand English and intend to travel to a country outside of Australia where JE is a risk within the next 6 months) and enrol in the study.

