### 1.3 Study population

The intention-to-treat (ITT) population will consist of all participants who were randomised to receive either the intervention or comparator, regardless of whether they reviewed their allocated intervention or completed the pre- and post-surveys. The only exclusion will be participants who withdraw their consent by exiting the pre-intervention survey prior to the material allocation stage.

The modified ITT population will consist of all participants who were randomised and provided both pre- and post-intervention data for the primary outcome.

Analyses for the primary and secondary outcomes will be conducted in the ITT and modified ITT populations, with the modified ITT analysis considered the principal analysis.

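### JE vaccinations received before enrolment can count as trial uptake, which inflates absolute uptake and pulls the uptake odds ratio towards 1

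*Combined protocol and SAP*

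**What the plan says.** **Who is in.** Protocol 5.1.1 lists four criteria, the last being "Planning travel to a JE-endemic region within the next 6-months". None concerns vaccination history. SAP 1.2 repeats them ("intend to travel to a country outside of Australia where JE is a risk within the next 6 months"). SAP 1.3 defines the principal population as "all participants who were randomised and provided both pre- and post-intervention data for the primary outcome"; neither that population nor the full ITT population refers to earlier vaccination.

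**What is known at baseline.** The pre-intervention survey (Protocol Appendix 4) asks "Have you ever received a JE vaccine" and carries on whatever the answer; a Yes only opens questions on brand and doses. The intention item in the same survey offers "I am already vaccinated" as a reply.

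**Intention.** Protocol 5.7.2 lists "those who are already vaccinated" as a fourth response group. SAP 2.9 makes the item binary: wanting the vaccine "is coded as 1, and all other responses are coded as 0". The outcome is a move from 0 before to 1 after.

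**Uptake.** The follow-up item is "Did you receive a vaccine for Japanese encephalitis before your trip". Its Yes options ask about brand, not date, and no option covers vaccination before the study. SAP Secondary Outcome 3 codes Yes as 1, and No or not remembering as 0. The logistic model adjusts for post-intervention intention, age and sex. Baseline vaccination status appears in no vaccination model as a covariate, restriction or sensitivity analysis.

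**Routing.** In the follow-up survey, people who saw no healthcare provider before travelling skip the uptake item, and those who did not go to a listed country never reach it.

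**The concern.** The SAP's uptake question is whether the decision aid raises pre-travel vaccination more than the fact sheet does. A dose given before randomisation cannot answer it, yet as worded and coded it scores as a success in either arm. Adding the same block of successes to both arms raises both proportions and shrinks the contrast between them.

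The two codings also sit badly together. Under the binary recode, one person can have intention 0 and uptake 1. The SAP adjusts uptake for intention because the two are strongly associated, and these participants weaken that association.

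What is at stake is the interpretation of a secondary outcome: a real effect on new vaccinations could be missed or understated, and the reported uptake percentages would mix old and new vaccinations. The primary decisional conflict analysis is not affected.

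**Working it through.** **The plan's own figure.** The documents give power only for the primary outcome (SAP 2.5). With effect size 0.30, correlation 0.5 and 175 per group, the residual SD is √(1 − 0.5²) = 0.866. Power is Φ(0.30 × √(175/2) / 0.866 − 1.96) = Φ(1.28) = 0.900, which matches the stated 90% to rounding. Recruitment is 350/0.70 = 500, as stated. I use 175 per arm below; the optional follow-up survey may yield fewer.

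**Crude uptake.** Let v be the share already vaccinated, all assumed to be asked and to answer Yes. Observed uptake in each arm is v + (1 − v)p, where p is true new uptake. I assume p = 10% (control) and 20% (decision aid), so the true OR is (0.20/0.80)/(0.10/0.90) = 2.25. Neither p nor v is in the documents. At v = 10%: control 0.10 + 0.90 × 0.10 = 0.19; decision aid 0.10 + 0.90 × 0.20 = 0.28; OR = (0.28/0.72)/(0.19/0.81) = 1.66.

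Power is Φ[(d − 1.96 × SE₀)/SE₁], where d is the difference in proportions, SE₀ the pooled standard error and SE₁ the unpooled one. The exclusion column uses 175(1 − v) per arm and the true 10% versus 20%.

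| v | Observed uptake | Crude OR | Power as planned | Power after exclusion | Control Yes answers that are old vaccinations |
|---|---|---|---|---|---|
| 0 | 10.0% vs 20.0% | 2.25 | 75% | 75% | 0% |
| 5% | 14.5% vs 24.0% | 1.86 | 62% | 73% | 0.05/0.145 = 34% |
| 10% | 19.0% vs 28.0% | 1.66 | 51% | 70% | 0.10/0.19 = 53% |
| 20% | 28.0% vs 36.0% | 1.45 | 36% | 65% | 0.20/0.28 = 71% |

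Exclusion gains power despite the smaller sample. The powers are for an unadjusted comparison.

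**Uptake adjusted for intention.** The SAP plans an adjusted OR, so I also fitted a logistic model to expected frequencies. Assumptions among those not already vaccinated: post-intervention intention 30% (control) and 45% (decision aid); uptake 5% in control non-intenders; intention OR 8; conditional treatment OR 1.80. The already vaccinated are coded intention 0, as the binary recode in SAP 2.9 would do. Age and sex are left out.

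| v | Adjusted OR, all answer Yes | Adjusted OR, half answer Yes |
|---|---|---|
| 0 | 1.80 | 1.80 |
| 5% | 1.65 | 1.70 |
| 10% | 1.57 | 1.62 |
| 20% | 1.49 | 1.51 |

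On the log scale at v = 10%, with all answering Yes, the adjusted OR loses 1 − ln 1.57/ln 1.80 = 23%. The crude OR loses 1 − ln 1.66/ln 2.25 = 37%. With all answering Yes, the fitted intention OR falls from 8.00 to 2.18 at v = 10%, which shows the weakened association.

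**Intention.** Observed positive change is (1 − v)p. Assume 20% versus 35% in those not already vaccinated, so OR = (0.35/0.65)/(0.20/0.80) = 2.15. At v = 10% the proportions are 18.0% and 31.5%, and OR = (0.315/0.685)/(0.18/0.82) = 2.10. The risk ratio stays at 1.75 and the risk difference goes from 0.150 to 0.135. Power goes from 88.5% to 83.6%, or 85.0% with exclusion.

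**The case against.** Several stronger readings are tempting, and the documents do not support them.

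- *That the trial would report the crude odds ratios above.* It would not: the SAP plans an adjusted OR, and on the assumptions here its loss is smaller. SAP Table 7 does not say whether intention enters as binary or with four categories; four categories would isolate most of the already vaccinated.
- *That every previously vaccinated person is counted as uptake.* Routing prevents this. Someone with no provider visit never sees the item, and SAP 2.2 says only that missing data are multiply imputed. How routing changes the mix of respondents cannot be worked out from the documents, so the tabulated percentages do not predict what the survey would yield.
- *That both vaccination outcomes are seriously diluted.* For intention the effect is small.
- *That these participants cannot respond to the aid at all.* The already-vaccinated reply is offered again afterwards, so a person can move from it to wanting a vaccine and count as a positive change. The survey records one dose, two doses or unsure, so earlier receipt need not settle the decision.
- *That the SAP contradicts the protocol on intention.* Protocol 5.7.2 lists four groups, but its outcome is the change in the proportion intending vaccination, which also sets intenders against everyone else.
- *That the comparison is biased towards a false positive.* Randomisation balances earlier vaccination in expectation.

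The background section of the protocol calls JE vaccine uptake in travellers poor, which gives no support for the upper end of the assumed range. All of this limits the size. None of it removes the gap: an undated question, a Yes coded as success, and no use of baseline vaccination status.

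**Conclusion.** The point holds for uptake, as attenuation, lost power and inflated absolute uptake in a secondary outcome. Vaccinations that predate randomisation can be scored as trial uptake, and the SAP has no rule to stop it.

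The direction is secure when prior vaccinees' Yes answers enter both arms alike. The size is not: it rests on an assumed 5% to 20% already vaccinated, assumed uptake rates and assumed answering behaviour. On those assumptions the crude OR falls from 2.25 to between 1.86 and 1.45, and the OR adjusted for binary intention from 1.80 to between 1.65 and 1.49. For intention the consequence is minor (OR about 2.15 to 2.10 at 10%), but the coding still pools the already vaccinated with people who do not want the vaccine. The change is worth making because it is cheap and the data it needs are collected before allocation.

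**What to change.** 1. Define baseline vaccination status from the pre-intervention survey alone, using both "Have you ever received a JE vaccine" and the intention reply "I am already vaccinated". The intention reply by itself would miss a previously vaccinated person who chose another answer. State in the SAP how the two items combine and how unsure replies are handled.
2. Restrict the uptake analysis to participants not already vaccinated at baseline, and apply the same restriction to the intention analysis. Allocation follows completion of this survey (Protocol 5.2), so the comparison stays randomised. Do not use the post-intervention reply to exclude anyone.
3. Report the all-participant versions as sensitivity analyses, and state in SAP Table 7 how post-intervention intention is coded.
4. Reword the follow-up item to ask about vaccination since the initial survey only if follow-up is still open. This is probably too late: the surveys point to recruitment towards the end of 2024 with follow-up at 3 to 6 months, and SAP version 3.1 is dated 13 November 2025. If follow-up data have already been analysed, label the restriction as added after the final SAP.

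The cost is SAP wording and a smaller denominator for two secondary outcomes (for example 157 or 158 rather than 175 per arm if 10% are already vaccinated). The restriction may also drop some people with an earlier dose who still want a vaccine; the sensitivity analysis keeps them in view. No new data are needed, and the primary analysis is unchanged.
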